#### **5.3.2 Secondary Objectives**

Differences between measurements in the three sets and/or five phases will be compared using the related-samples Friedman's two-way analysis of variance by ranks and visualized by simple box plots according to set/phase.

Subgroup analyses by gender, BMI, and exploratory analysis of factors influencing the correlation of DTF, ITF and the oesophageal pressure fluctuation.

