#### **3.3 Total Number of Subjects Projected**

The aimed number of included healthy subjects is 50.

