### **4.2 Measurement Period**

**Setup** Subjects take part in the study once. Participants will be seated on a semi-recumbent bicycle ergometer during the whole experiment. At the beginning, participants will be asked to determine their ergometry exercise loads to achieve perceived exertion equivalents to Borg scale 10 (fairly light) and 15 (hard). Participants will undergo three sets of 5 study phases each. The order of the study phases will be randomly assigned, but with the same order of phases in each set.

- First set: seated on the ergometer, but resting
- Second set: ergometry with perceived exertion Borg scale 10
- Third set: ergometry with perceived exertion Borg scale 15

As mentioned above, each set is subdivided into an identical order of 5 study phases. The order of phases is randomly assigned prior to the start of the experiment. The 5 different phases are:

- Without connection to a respirator (phase null)
- Connected to a respirator with PEEP and Psupp of 0 cmH2O (phase P0S0)
- Connected to a respirator with PEEP of 5 cmH2O and Psupp of 0 cmH2O (phase P5S0)
- Connected to a respirator with PEEP of 5 cmH2O and Psupp of 5 cmH2O (phase P5S5)
- Connected to a respirator with PEEP of 5 cmH2O and Psupp of 10 cmH2O (phase P5S10)

The DTF, ITF, airway and oesophageal pressures as well as minute volume, blood pressure, heart rate and SpO2 will be recorded at the end of each study phase.

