### **4.4 Subject Completion/Withdrawal**

Subjects may withdraw from the study at any time. They may also be discontinued from the study at the discretion of the investigator for lack of adherence to study measurements. The

Investigator may exclude participants from this study to protect the subject for reasons of safety or for administrative reasons. It will be documented whether or not each subject completes the clinical study. If the Investigator becomes aware of any serious, related adverse events after the subject completes or withdraws from the study, they will be recorded in the source documents and on the CRF.

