### **5.2 Secondary Endpoints**

The secondary objectives are to determine the influence of increased respiratory effort induced by exercise on absolute values of the index tests and their relationships. Another secondary objective is to assess the effect of different levels of respiratory support (spontaneous breathing, CPAP, pressure support) on DTF, ITF and oesophageal pressure swings.

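### Friedman's test handles one condition factor, so it cannot analyse exercise load and support level jointly in this 3 x 5 within-participant design or estimate their effects

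*Protocol*

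**What the plan says.** On design, Protocol section 4.2 says "Participants will undergo three sets of 5 study phases each". The sets are rest, Borg 10 and Borg 15, listed as first, second and third. The phases are five levels of respiratory support, from no respirator to PEEP with pressure support. On sequence it says "The order of the study phases will be randomly assigned, but with the same order of phases in each set". Section 3.3 aims for 50 participants.

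On objectives, section 5.2 asks for the "influence of increased respiratory effort induced by exercise on absolute values of the index tests and their relationships". As a separate objective, it asks to "assess the effect of different levels of respiratory support (spontaneous breathing, CPAP, pressure support) on DTF, ITF and oesophageal pressure swings". Section 2.2 has similar wording.

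On method, section 5.3.2 reads "Differences between measurements in the three sets and/or five phases will be compared using the related-samples", continuing "Friedman's two-way analysis of variance by ranks and visualized by simple box plots according to set/phase". No other test or model is named for set and phase differences. Section 4.4 lets participants withdraw at any time and lets the investigator discontinue them.

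**The concern.** The two ways in the test's name are the participant (the block) and a single condition factor. They are not load and support. The protocol has two crossed condition factors and names a test for one, and the and/or wording leaves open which one-factor comparison will be run.

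The secondary objectives ask for an effect and an influence, which are quantities. Friedman's test gives a p-value for some difference among ranked conditions, without a magnitude or interval. It also has no place for a covariate such as phase position, and in its standard form it needs every condition of the test observed in each participant. The trial could therefore collect 15 measurements per person and still report little on how far support or exercise shifts DTF, ITF or oesophageal pressure swing.

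**Working it through.** The protocol gives no significance level, effect size, standard deviation or missing-data rate for these comparisons, so there is no figure of its own to reproduce. The check has four steps.

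**1. Ways to run the test.** Inputs: 3 sets, 5 phases (section 4.2) and 3 outcomes (section 5.2).
- Slices: sets compared within each phase (5 tests) plus phases compared within each set (3 tests) = 8 per outcome; 8 x 3 = 24.
- Averages: sets after averaging over phases, or phases after averaging over sets.
- One factor with 3 x 5 = 15 levels and 14 degrees of freedom, ignoring the structure.

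None of these contains a load-by-support term. Finding significance in one slice and not in another is not a test that the two slices differ.

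**2. What the test can distinguish.** Simulation, 1,000 runs per scenario, 50 participants. Assumed: participant SD 1, residual SD 0.5, load effects 0, 0.5 and 1.0, support effects 0, 0, -0.1, -0.3 and -0.5. In the last scenario the support effect is scaled by 0.2, 1 and 1.8 across loads, with the same marginal means. Rejection rates at 5%:

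| Scenario | Friedman, 15 cells | Friedman, sets (averaged) | Friedman, phases (averaged) | Two-factor interaction test |
|---|---|---|---|---|
| No effects | 4.3% | 4.2% | 4.1% | 4.1% |
| Load only | 100% | 100% | 5.4% | 6.2% |
| Load and support, additive | 100% | 100% | 100% | 4.6% |
| Support effect grows with load | 100% | 100% | 100% | 100% |

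The first row shows that Friedman's test keeps its error rate as a one-factor test. The last two rows show that these Friedman tests respond alike to two different patterns. The 100% figures reflect large assumed effects and are not power estimates for this trial.

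**3. Phase position.** Five phases have 5! = 120 possible orders, more than the 50 participants, so randomisation balances position only on average. Because the order repeats in each set, a position effect does not average out within a participant. Friedman's test cannot adjust for it.

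**4. Incomplete participants.** If each measurement is missing independently with probability m, a test over k conditions keeps 50 x (1 - m)^k participants:

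| Assumed m | k = 3 | k = 5 | k = 15 |
|---|---|---|---|
| 1% | 48.5 | 47.5 | 43.0 |
| 2% | 47.1 | 45.2 | 36.9 |
| 5% | 42.9 | 38.7 | 23.2 |
| 10% | 36.5 | 29.5 | 10.3 |

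The result depends strongly on the pattern. At an assumed 3% independent loss, the 15-cell test loses 1 - 0.97^15 = 37% of participants. If the same 3% (0.03 x 750 = 22.5 measurements) came from whole missed Borg 15 sets of five, it would lose 22.5 / 5 = 4.5 participants, or 9%, and phase comparisons at rest or Borg 10 would lose none.

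**The case against.** The strongest reply is that the plan works as it stands. The and/or wording permits valid one-factor comparisons that partly serve both the exercise and the support objective. The comparisons are secondary, in a physiological study of healthy volunteers, and the primary analysis uses repeated measures correlation. Paired differences with intervals, and rules for missing data, could be added in a statistical analysis plan without removing Friedman's test. All of this stands and limits the weight of the point. It does not supply a joint analysis, because the protocol itself names the test.

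Several stronger readings are tempting, and the documents do not support them:
- *The interaction is a stated objective.* It is not. Sections 2.2 and 5.2 ask how exercise affects the values and the relationships between measures and, separately, how support affects the values. Whether support acts differently under load is a useful question that the design allows. Friedman's test on single measures does not address the relationships either.
- *Power is lost.* Under normality the test's relative efficiency is 3k/(pi(k+1)): 0.72, 0.80 and 0.90 for k = 3, 5 and 15. For double-exponential data it is 3k/(2(k+1)): 1.13 for k = 3 and 1.25 for k = 5, which favours Friedman. The protocol gives no distribution.
- *A false positive is likely.* With 24 independent true nulls at 5%, 1 - 0.95^24 = 71%. But the outcomes are correlated, exercise is meant to change them, and a mixed model with many contrasts runs no fewer tests.
- *Hard exercise will remove many participants.* No rate is given, and participants set their own load for Borg 15. Section 4.4 speaks of "They may also be discontinued from the study at the discretion of the investigator for lack of adherence to study measurements", which does not describe stopping hard exercise.

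**Conclusion.** The point holds in this form: the only test named for set and phase differences handles one factor, while the design has two crossed factors. However it is run, it gives no joint analysis of load and support, no effect size with an interval and no adjustment for phase position, and it excludes a participant from any test in which a needed cell is missing.

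The mismatch follows from the structure of the test and needs no assumption. The simulated contrast (4.6% against 100% for the interaction test; 100% in both for the Friedman tests) rests on assumed effects and illustrates it. The cost in participants cannot be sized from the protocol. The planned comparisons are valid, and the primary analysis is untouched. This is an inexpensive improvement to the secondary analyses that is worth making; it does not invalidate them.

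**What to change.** In section 5.3.2, make the main analysis one linear mixed model for each of DTF, ITF and oesophageal pressure swing, on the log scale if skewed:
- **Fixed effects:** set, phase, set x phase, and position of the phase within its set. The position term assumes that each participant receives their own random order; section 4.2 should say so, because a single common order would make position and phase inseparable.
- **Participant effects:** let responses to set and phase vary between participants, or use a robust or unstructured covariance. A random intercept alone could understate standard errors if people respond differently; section 5.4 already reports inter-individual differences in the pilot.
- **Data:** all recorded phases.
- **Reporting:** a short prespecified list of contrasts with 95% confidence intervals, such as P5S5 and P5S10 versus P5S0, and Borg 10 and Borg 15 versus rest. Averaged over the other factor, that is 4 contrasts x 3 outcomes = 12. Giving the two support contrasts separately at each load would take 2 x 3 x 3 = 18, so the list should be kept short and either labelled secondary or adjusted for multiplicity.
- **Sensitivity:** keep Friedman's test, stating which comparison is run.

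The cost is revised wording, slightly more analysis work and reliance on model assumptions, which the log scale and the rank-based check help to address. Two limits remain. The sets are listed in a fixed sequence, so the load contrasts still carry any effect of time in the session. These models also do not answer the objective on relationships between the measures.

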### **5.4 Sample Size and Power**

In a previous pilot experiment with 23 participants, we studied the correlation of DTF and oesophageal pressure swings, where we found a moderate correlation and fair discrimination between exercise loads of DTF and oesophageal pressure swings (not yet published). Furthermore, we observed inter-individual differences in the DTF/oesophageal pressure relationship, that might be explained by habitus, BMI or gender. However, the small sample size prevented any meaningful evaluation of this question. No other comparable studies exist for this study question. Formal sample size determination cannot be calculated, the authors conjecture that 50 participants will be needed to adequately control for confounding factors.

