### **5.3 Statistical Methods**

#### **5.3.1 Primary Objective**

Oesophageal pressure swings are used as the comparator for respiratory effort. Correlations with DTF and ITF will be assessed by calculating repeated measures correlation coefficient. Correlations of DTF and ITF will be additionally visualized using clustered box plots.

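### The reason given for 50 participants, control of confounding, does not fit the primary repeated measures correlation; the pilot's question is effect modification, better tested by interaction terms than by subgroups

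*Protocol*

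**What the plan says.** Section 3.3 sets the size: "The aimed number of included healthy subjects is 50". Section 5.4 explains it by a pilot: "In a previous pilot experiment with 23 participants, we studied the correlation of DTF and oesophageal pressure swings". The pilot result is given in words only: "we found a moderate correlation and fair discrimination between exercise loads of DTF and oesophageal pressure swings". The pilot team also reports that "we observed inter-individual differences in the DTF/oesophageal pressure relationship, that might be explained by habitus, BMI or gender", and that 23 people were too few to evaluate this. The section then concludes: "Formal sample size determination cannot be calculated, the authors conjecture that 50 participants will be needed to adequately control for confounding factors".

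The primary analysis in 5.3.1 is: "Correlations with DTF and ITF will be assessed by calculating repeated measures correlation coefficient". No covariate or adjusted model is named there or elsewhere.

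BMI and gender enter the analysis only in 5.3.2: "Subgroup analyses by gender, BMI, and exploratory analysis of factors influencing the correlation of DTF, ITF and the oesophageal pressure fluctuation". Section 2.2 makes the identification of such factors a secondary objective.

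On the amount of data per person, section 4.2 states: "Participants will undergo three sets of 5 study phases each".

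**The concern.** The sample size is defended by a property that the planned primary analysis does not take from it. Gender, BMI and habitus do not change during one short session. A repeated measures correlation works on deviations from each person's own mean, so a constant difference between people drops out at any sample size. If a trait changes the slope of pressure on DTF, that is effect modification. More participants estimate it better but do not control it away.

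Two things follow. The reader is not told what 50 participants deliver, either for the primary coefficient or for the moderator question that prompted the number. And that moderator question is assigned to subgroup analyses, which can be a poor tool for it. A null subgroup result could be read as showing that BMI and gender do not matter, and a spurious one as showing that they do.

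**Working it through.** **Inputs from the protocol.** n = 50 (3.3); pilot n = 23 (5.4); 3 × 5 = 15 measurements per person (4.2). No alpha, power, effect size or precision target is stated, so 50 cannot be reproduced or refuted.

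**Assumptions.** Two-sided 5%, 80% power. Within-person r = 0.5 for the unquantified pilot correlation, with range 0.3 to 0.7. In simulations: 15 measurements per person, mean slope 0.577 and residual SD 1 (which gives r = 0.5), and between-person slope SD of 0, 0.3 or 0.5.

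**1. What the primary coefficient removes.** Adding large person-level shifts to both variables left the repeated measures correlation at 0.4515, while the pooled Pearson correlation became 0.94. Constant level differences do not reach the primary coefficient.

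**2. What a larger n does about slope differences.** With slope SD 0.5 the mean coefficient was about 0.46 at n = 23, n = 50 and n = 500 alike, against 0.50 with a common slope. Sample size does not change this.

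**3. Precision of the primary coefficient.** Degrees of freedom = n × (15 − 1) − 1, so 699 at n = 50 and 321 at n = 23. Interval = tanh(atanh r ± 1.96/√(df − 1)).

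| assumed r | n = 50 | n = 23 |
|---|---|---|
| 0.3 | 0.23 to 0.37 | 0.20 to 0.40 |
| 0.5 | 0.44 to 0.55 | 0.41 to 0.58 |
| 0.7 | 0.66 to 0.74 | 0.64 to 0.75 |

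These are nominal. At n = 50 and slope SD 0.5, the simulated standard error was 0.056 against a nominal 0.030, so the total 95% width is about 2 × 1.96 × 0.056 = 0.22 rather than 0.12.

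**4. Detectable moderators at n = 50.**
- BMI against individual slope: tanh((1.96 + 0.8416)/√47) = 0.39. Power at r = 0.3 is 56%.
- Gender, 25 against 25, two-sample t test on individual slopes: d = 0.81. Power at d = 0.5 is 41%.

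**5. Comparing subgroup correlations, 25 against 25.** Share of simulated trials with p < 0.05:

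| scenario | correlations (Fisher z) | individual slopes |
|---|---|---|
| no group difference, slope SD 0.3 | 16% | 5% |
| no group difference, slope SD 0.5 | 29% | 5% |
| slope 1.5 times larger, noise scales with it (same r), slope SD 0 | 5% | 77% |
| slope 1.5 times larger, constant noise, slope SD 0 | 87% | 94% |

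The first two rows are false positives. The third is a real slope difference that the correlations cannot see. The fourth is the case in which comparing correlations works well.

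**6. Grouping BMI.** If BMI is normal and is split at the median, the retained information is 2/π = 0.64, and 0.64 × 50 = 32 participants' worth.

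**The case against.** The strongest reply is that 5.4 never says the 50 are for the repeated measures correlation. Read in sequence, it says that the pilot could not explain differences between people and that more people are needed for this, which is the secondary objective in 2.2. That reading is fair. What remains is that the word used is confounding, no analysis in the protocol adjusts for anything, and neither the primary precision nor the detectable moderator size is stated.

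A reader might also infer that the protocol is wrong to say that a formal calculation is impossible, since a pilot exists. The documents do not support that. The primary question is what ITF adds to DTF. The pilot reported DTF and pressure only, ITF has not been tested during NIV according to section 1, and no numerical r is given. A precision statement under assumptions is possible and useful, but it is not the formal sizing of that question.

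A reader might infer, too, that fixed traits can never confound the coefficient. That goes too far. If a trait alters how both DTF and pressure respond to exercise load, within-person correlation can arise without a direct link. In a simulation of 50 people with 15 measurements and residual SD 1, a trait-by-load effect on both variables gave a mean coefficient of 0.15 (effect 0.5) or 0.41 (effect 1.0). Load is varied by design here. A larger n alone does not cure this either.

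Finally, 5.3.2 names no subgroup statistic and no BMI cut, and its exploratory factor analysis could be an interaction model in an SAP that is not shown. The criticism of subgroup correlations is therefore conditional, and the fourth row of the table shows that they are not always weak.

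**Conclusion.** The stated rationale does not match the planned primary analysis. Controlling constant traits is something the repeated measures correlation does at any n, and slope differences are not removed by 50 participants or by 500. The question the pilot raised is effect modification. For that question 50 participants have 80% power only for fairly large effects, about |r| = 0.39 for BMI or d = 0.81 for an even gender split.

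If the subgroup analyses in 5.3.2 compare correlation coefficients, false positives of about 16% to 29% are to be expected under slope SDs of 0.3 to 0.5, and a slope difference that leaves r unchanged would be missed. Grouping BMI would lose information besides.

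The number 50 is not shown to be wrong, and the nominal precision of the primary coefficient is good under a common slope. The figures rest on an assumed r, assumed slope variation and assumed subgroup sizes, because the protocol gives none of these. The point deserves correction before analysis, but it does not threaten the study.

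**What to change.** **Section 5.3.2.** Test moderation in a mixed model to be added to the plan (the protocol has none at present). Use oesophageal pressure swing as the outcome, with a random intercept and a random slope per participant, and interaction terms DTF × BMI (continuous) and DTF × gender. Do the same for ITF. Report the interactions with 95% CIs and keep them labelled exploratory.

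**Section 5.4.** Replace the confounding rationale with one of effect modification. State, with the assumptions, what 50 participants give:
- a nominal 95% CI of about 0.44 to 0.55 at a within-person r of 0.5 (0.23 to 0.37 at 0.3; 0.66 to 0.74 at 0.7), wider if slopes vary between people;
- 80% power for moderator effects of about |r| ≥ 0.39 (BMI with individual slope) or d ≥ 0.81 (25/25 gender split), so smaller effects are not excluded.

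The pilot's numerical correlation, which the sponsor holds, should replace the assumed 0.5 for DTF; the value for ITF remains an assumption.

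**Cost.** Wording in two sections, a slightly more complex model, and a less favourable but accurate statement on moderators. No extra participants: keep 50.

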## **5.5 Interim Analysis**

No interim analysis is planned.

## **6 SAFETY MANAGEMENT**

### **6.1 Clinical Adverse Events**

Clinical adverse events (AEs) will be monitored throughout the study.

### **6.2 Adverse Event Reporting**

Since the study procedures are not greater than minimal risk, AEs are not expected. If any unanticipated problems related to the research involving risks to subjects or others happen during this study (including AEs) these will be reported to the chief investigator. Through discussion of the study team, it will be decided whether any AE may be linked to any of the study measures, and whether exclusion of the participant or discontinuation of the study must be undertaken.

## **7 STUDY ADMINISTRATION**

### **7.1 Data Collection and Management**

Source documents are where data are first recorded, and from which participants' CRF data are obtained. All documents will be stored safely in confidential conditions. On all trial-specific documents, other than the signed consent, the participant will be referred to by the trial participant number/code, not by name.

Information will be collected by a study investigator for each participant using a data collection form. The form will be stored in the clinical report file (CRF). The participants will be identified by a unique trial specific number in any database. The name and any other identifying detail will NOT be included in any trial data electronic file.

No data, forms, or other records will leave the site to maintain confidentiality. All records will be kept in a locked file cabinet. All computer entry and networking programs are secured with personalized passwords. Data will be retained for 10 years on the institutions premises and will afterwards be deleted.

Participants are given the option to be approached for future research, this is contained in the consent form. Those contact details are held securely, separately from the research data, and kept updated.

